### Power Analyses and Sample Size Considerations

Given variability in EMA adherence, we conducted power analyses for 100 participants, while planning to recruit 130 participants to account for those with inadequate compliance. Most study aims will be tested using dynamic structural equation modeling, as described herein. In a recent Monte Carlo simulation study [90], adequate power (>0.80) for modeling of a single process (eg, SI) was demonstrated for moderate effects where n=100 with as few as 50 repeated measures (*t*=50). Thus, this study (*t*=196, 7 prompts per day for 28 days) is well powered even with a compliance rate as low as 57.1% (112/196; 4 prompts per day for 28 days) to examine within-person processes (H1a, H1b, and H2b). To provide more conservative estimates of power, a series of simulations with 100 replications were conducted for a random-effects (multilevel) logistic outcome using R software (The R Foundation for Statistical Computing) [91]. The assumptions for these simulations were as follows: (1) n=100, (2) within-person effects for all predictors, (3) standard normal distributions for all predictors, and (4) an intercept variance of 0.3. On the basis of these models, the study is well powered (>0.8) to detect standardized within-person effects as low as 0.1 with compliance as low as 64%.

For H2a, we used G*Power (Heinrich Heine University) [92] to conservatively determine the minimum detectable effect predicting any SA over follow-up with n=100, Cronbach α=.05, and β=.8, controlling for a moderate effect of SI on SA (0.3). We assumed an event proportion of 10% for the outcome based on recent literature [93]. On this basis, the study is powered to detect an odds ratio >2.63 for the effect of baseline emotion-related impulsivity or inhibitory control on follow-up SA risk. By way of comparison, recent research has demonstrated significant predictors of follow-up SA risk with odds ratios from 6 [94] to 13 [93].

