#### Intensive Longitudinal Protocol

During the baseline session, participants will be asked to provide their typical wake times and bedtimes, as well as any specific windows of time in which they will be unavailable to answer surveys (for instance, work shifts in which they are not allowed to access their phone), which are then used to schedule the EMA survey distribution. Participants who do not own a mobile phone capable of accessing the internet will be provided with a *loaner* phone to use for the EMA surveys; other participants will use their own mobile phone. All participants will be walked through practice EMA items to familiarize them with the structure of the EMA surveys and the mobile version of the Emotional Stop-Signal Task before discharge.

The EMA surveys will be distributed using a proprietary distribution system that integrates with Amazon Web Services’ Simple Notification Service system to send SMS text messaging notifications of survey availability. These notifications will include a link to a Qualtrics survey that will be available for 30 minutes only after each notification.

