**All surveys**		
	Current suicidal ideation	2
	Current urges for nonsuicidal self-injury	2
	Current negative affect	6
	Current positive affect	2
	Current hopelessness	1
	Current agitation	2
	Current emotional pain	2
	Current defeat	2
	Current entrapment	2
	Current self-criticism	2
	Current suicide capability	4
	Current physical pain interference	1
	Current belongingness	2
	Current burdensomeness	2
	Current perceived emotional support	2
	Current perceived practical support	2
	Since last survey: suicidal behavior	1
	Since last survey: nonsuicidal self-injury	1
	Since last survey: stressors	3
	Since last survey: complimented or praised	1
	Since last survey: alcohol use	2
	Since last survey: drug use	4

At baseline, participants will also be provided with the actigraphy device (wActiSleep-BT; ActiGraph, LLC) and instructed on how to wear it during the follow-up period. Participants will be asked to wear the device as much as possible for 28 days after discharge. The device continuously records activity through accelerometer (approximately 30-hertz data sampling with timestamps) with a single charge typically exceeding 28 days [96]; however, participants will also be provided with a charger and asked to charge the device at least twice during follow-up at times when the watch would not otherwise be worn, such as when bathing. The device continuously records data to provide valid scores for a variety of indices, including sleep duration, sleep onset latency, total awakenings, length of awakenings, overall sleep efficiency, intensity of movement during sleep awakenings, and light exposure during sleep [97]. Participants will be provided with a self-addressed, postage-paid envelope to return the actigraphy device, charger, and loaner phone (if applicable) to the research team after study completion.

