#### Data Analysis Plan

Before conducting analyses, we will clean and check data for errors, address outliers, ensure that statistical assumptions for analyses have been met, and examine potential confounders to include in subsequent analyses as warranted. Variables that may exhibit skewness (eg, number of lifetime episodes of NSSI) will be examined for skewness and kurtosis and, if necessary, either rank transformed or log transformed. We will include the effect of time (196 prompts over 28 days) to account for habituation and examine potential nonlinear effects of, for instance, age. Most analyses will use time-series (dynamic) structural equation modeling [98,99], which uses Bayesian estimation, conducted with MPlus statistical software (Muthén & Muthén) [99]. Dynamic structural equation modeling is robust with regard to high rates of missing data, zero-inflated categorical variables, and variable time intervals among observations, all of which are common in EMA with these types of data, and allows for latent decomposition of constructs into their constituent between- and within-person components [98]. Dynamic structural equation modeling also facilitates within-person lagged analyses to examine prospective relationships between time *t* predictors and time *t*+1 outcomes; by controlling for autoregressive effects over time, these methods can model within-person change in constructs over time.

For H1a, we will examine whether within-person changes in negative affective experiences precede proximal within-person changes in SI using 2-level random slope models. Each of 7 momentary negative affective experiences reported at time *t* will be regressed on itself at time *t–*1, producing a measure of residualized change in each negative affective experience. Momentary SI reported at time *t* will be regressed on itself at time *t–*1, as well as the 7 negative affective experience change indicators, yielding an estimate of the within-person effect of changes in all negative affective experiences on subsequent within-person changes in SI, controlling for autoregression. For H1b, we will examine the within- and between-person factor structures of the 7 negative affective experiences using multilevel exploratory factor analysis [100]. Using established best practices, we will identify the most appropriate structure and use these within-person factors to predict changes in SI over time, similar to the procedures used for H1a.

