For H2a, we will estimate the effects of baseline emotion-related impulsivity and inhibitory control on odds of SA over follow-up, controlling for between-person differences in SI severity. To do this, person-mean estimates of SI and person-maximum estimates of SA (yes or no) will be calculated using EMA data. SA can then be predicted by baseline emotion-related impulsivity and inhibitory control scores using logistic regression analysis, controlling for participants’ SI severity. For H2b, we will then test whether within-person changes in state inhibitory control precede subsequent SA among individuals reporting SI. Using a 2-level random slope model, we will model time *t* inhibitory control (controlling for inhibitory control measured at time *t–*1) as a predictor of time *t*+1 SA, controlling for time *t* SI.

For sleep-related hypotheses, we will use 2-level random slope models, as described previously, but in which survey-level data on SI and SA have been pooled to create day-level variables (because sleep varies at the daily, but not survey, level). For H3a, we will use person-mean–centered total sleep time on day *d–*1 to predict next-day (day *d*) SI, controlling for day *d–*1 SI. Models for H3b will parallel those used to test H2a, whereby total sleep time on day *d*-1 will be used to predict next-day SA (day *d*), controlling for day *d* SI. For H3c, we will test whether the sleep-SA association (H3b) is mediated by within-person changes in inhibitory control. Building on the H3b model, we will add in the effect of sleep on day *d–*1 predicting inhibitory control on day *d*. To ensure that we are capturing sleep-related changes in inhibitory control, inhibitory control on day *d* will also be regressed on inhibitory control measured on day *d–*1. Finally, day *d* inhibitory control will be used to predict day *d* SA, controlling for day *d* SI. Indirect and direct effects will be calculated and tested for significance using the MPlus *model indirect* command.

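### H2b pairs a reported attempt with the preceding prompt, but the attempt item looks back to the last survey, so after missed prompts the predictor is unobserved and can fall after the attempt

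*Protocol article*

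**What the plan says.** The Data Analysis Plan states the aim of the within-person part of H2b as a question of order: "test whether within-person changes in state inhibitory control precede subsequent SA among individuals reporting SI". The model takes inhibitory control at time t, adjusted for its value at t–1, "as a predictor of time *t*+1 SA, controlling for time *t* SI".

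Four other statements determine what t and t+1 mean in the data:

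- **Time index.** The Power Analyses section sets the number of time points at 196, from seven prompts a day over 28 days. The Data Analysis Plan uses the same count for its time trend: "We will include the effect of time (196 prompts over 28 days").
- **Outcome.** The only EMA item in Table 2 from which an attempt can be coded is "Since last survey: suicidal behavior". It is a single item, and the table lists none for when the behavior took place.
- **Survey window.** Under Intensive Longitudinal Protocol, each link is "available for 30 minutes only after each notification". The stop-signal task is done after the survey, so a missed prompt yields neither a task score nor an SI rating.
- **Compliance.** The Power Analyses section counts H2b among the well-powered analyses at a "compliance rate as low as 57.1% (112/196; 4 prompts per day for 28 days"). For the multilevel logistic simulations it claims adequate power "with compliance as low as 64" percent. The Compensation section sets a bonus at 75% (147/196).

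**The concern.** The lag in H2b counts prompts, but the outcome is dated by when it is reported. The two agree only when no prompt is missed around the attempt. Suppose an attempt occurs between two prompts and the later prompt is missed. The attempt then enters the data at the next completed survey, perhaps several prompts on. A lag of one prompt pairs it with the prompt just before that report. That prompt was missed, so inhibitory control and SI have no values there, and it comes after the attempt.

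The article's answer to non-response is that dynamic structural equation modeling copes with missing data and uneven intervals. That addresses the empty predictor cell. It does not move the attempt back to the interval in which it happened. What is at stake is the temporal claim itself: H2b is meant to show that a lapse in control comes first, and for part of the events the pairing runs the other way.

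**Working it through.** **The plan's own figures.** 7 × 28 = 196. 4 × 28 = 112, and 112/196 = 57.1%. 147/196 = 75%. All agree with the article. It gives no figure for the share of attempts that would be misaligned.

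**Set-up.** Let p be compliance, with prompts missed independently of one another and of the attempt. Let participants read *last survey* as the last one they completed. An attempt falls between prompts k and k+1 and is reported at the first completed prompt from k+1 onward. Time t is the prompt just before that report.

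- If k+1 is completed (probability p), time t is prompt k, which precedes the attempt. Its score exists if k was also completed, so the score at t is observed with probability p².
- If k+1 is missed (probability 1–p), time t is k+1 or later. It falls after the attempt and is itself a missed prompt.
- Unobserved in total: (1–p) + p(1–p) = 1–p². Share of these that fall after the attempt: (1–p)/(1–p²) = 1/(1+p).

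| Compliance p | t after the attempt, 1–p | t unobserved, 1–p² | t observed, p² | After, among unobserved |
|---|---|---|---|---|
| 57.1% | 42.9% | 67.3% | 32.7% | 63.6% |
| 64% | 36.0% | 59.0% | 41.0% | 61.0% |
| 75% | 25.0% | 43.8% | 56.3% | 57.1% |

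A simulation of 20,000 attempts per level agreed within one percentage point. With clustered missingness (lag-1 correlation 0.3 and 0.5), the share after the attempt hardly moved: 43.1% and 42.9% at 57.1% compliance, 25.5% and 25.6% at 75%. The unobserved share fell, to 60.2% and 55.4% at 57.1% compliance and to 38.8% and 35.2% at 75%.

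**Effect on the estimate (illustration).** The inputs here are assumptions, not figures from the article: a true log-odds of 0.5 per SD, autocorrelation of inhibitory control of 0.1 to 0.5, a simple logistic model, and the score at t treated as known even where it would be missing. Ranges run over the autocorrelations.

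| Compliance | Preceding scheduled prompt | Last completed survey | Adjacent completed prompts only |
|---|---|---|---|
| 57.1% | 0.31–0.35 | 0.31–0.38 | 0.51–0.54 |
| 64% | 0.32–0.37 | 0.34–0.38 | 0.48–0.51 |
| 75% | 0.41–0.45 | 0.39–0.46 | 0.50–0.52 |

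Pairing with the last completed survey secures the order of events but leaves about the same attenuation, because the lag varies. In a separate simulation of that pairing, adding elapsed time as a main effect changed the estimate by no more than 0.005. Only the adjacent-prompt subset came back to about 0.5.

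**The case against.** The strongest reply is that the article never says what t counts in the H2b lag. The 196 in the power section is set against a benchmark of 50 repeated measures, and 112 completed surveys are treated as enough, so t could be read as measurements obtained. The 196 in the analysis section belongs to a time trend. If t counts completed surveys, the predictor is observed wherever the task was done, and it precedes the recall window by construction. This stands as a condition on the finding. Both places where the article gives t a number count scheduled prompts, so that reading is better supported. Even under the other reading, one lag could span hours or days, and the article should say so.

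A second reply is that this is detail for the full plan. The exact items, the interview content and the contact procedures are in a preregistration not shown here. But the article itself fixes the lag, the prompt count and the look-back item, and together these produce the misordering. The contact within 24 hours of a report and the 4- and 8-week interviews might date an attempt, but neither is said to re-date the H2b outcome.

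Some stronger readings are tempting and are not supported:

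- *The predictor is imputed for most attempts.* With independent missingness this holds at 57.1% and 64%, but not at 75%. The article gives the two lower figures as floors for power, not as expected compliance.
- *The test cannot show precedence.* At these compliance levels time t still precedes the attempt in 57%, 64% and 75% of cases. The illustration shows attenuation, not an uninformative test.
- *Scores measured after an attempt are entered as its predictor.* In every such case the prompt was missed, so no score measured there exists.
- *Non-response rises after an attempt, making this worse.* The documents say nothing on this, and the finding does not need it.
- *Only about three attempts would have a usable score.* That borrows the 10% event proportion given for H2a and adds an assumed one attempt per person.

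**Conclusion.** The point holds, on the condition that t in H2b counts scheduled prompts. At the article's own compliance figures of 57.1%, 64% and 75%, the prompt used as predictor falls after the attempt for 43%, 36% and 25% of EMA-reported attempts. It has no score for 67%, 59% and 44%. These are nested shares, not separate groups. The figures further assume that *last survey* is taken as the last one completed and that non-response is unrelated to the attempt. Clustered non-response lowers the unobserved share and leaves the share after the attempt almost unchanged. The H2b estimate is likely attenuated and its claim of precedence weakened, though not emptied. The amount of attenuation is illustrative only.

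**What to change.** Before analysis begins, state for H2b:

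1. Inhibitory control and SI are taken from the last completed survey before the recall window of the survey that reports the attempt, so the predictor precedes the attempt by construction.
2. The inhibitory-control effect may vary with the time elapsed to the report, through an interaction. A main effect of elapsed time alone does not deal with the varying lag.
3. A sensitivity analysis is limited to adjacent completed prompts.
4. Where the contact within 24 hours or a follow-up interview happens to give the date of an attempt, it is placed in the interval where it occurred.

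The first three steps use data already planned: a data-preparation rule, an interaction and one extra analysis. The fourth depends on whether dates are recorded, which the article does not say. The cost is a lag of varying length, and the estimate from last-completed pairing may still be attenuated. The adjacent-prompt analysis keeps only about p² of reported attempts: 33% at 57.1% compliance and 56% at 75%.

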### Hypotheses

The goal of this study is to integrate examination of affective, cognitive, and physiological risk factors for short-term changes in suicidal thinking and suicidal behaviors among adults known to be at high risk within an ideation-to-action framework. To that end, our hypotheses are as follows:

Hypothesis 1a (H1a): within-person increases in affective suicide risk factors conceptually related to psychache (negative affective experiences) will individually precede within-person increases in SI.Hypothesis 1b (H1b): negative affective experiences will co-occur in daily life such that they are best conceptualized as indices of a single latent construct capturing emotional distress (psychache), which will itself predict short-term increases in SI.Hypothesis 2a (H2a): among those with SI, higher baseline self-reported emotion-related impulsivity will predict greater odds of SA over follow-up.Hypothesis 2b (H2b): among those with SI, poorer baseline behavioral indices of inhibitory control in the context of negative affective stimuli will predict greater odds of SA over follow-up. We also predict that, among those with current SI during EMA, lower EMA-assessed inhibitory control will prospectively predict subsequent SA.Hypothesis 3a (H3a): during the EMA protocol, short sleep duration will predict within-person increases in SI.Hypothesis 3b (H3b): during the EMA protocol, short sleep duration will predict greater risk of next-day SA among those with SI.Exploratory hypothesis 3c (H3c): the within-person effects of short sleep duration on SA will be mediated by within-person changes in inhibitory control assessed during EMA.

A visual depiction of these hypotheses is provided in Figure 1.

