Participants will receive 7 pseudorandom notifications between specified wake times and bedtimes, avoiding the blackout windows specified by the participant. We will add 15 minutes to the wake time to avoid missed surveys because of variability in wake times as well as to ensure that participants will be able to respond effectively to items regarding affect and related constructs after waking. Notifications will be randomized by *binning* the participants’ available hours into 7 equal windows and then randomly choosing a survey time within each bin. Notifications cannot occur within 30 minutes of another notification. If participants do not click the survey link within 10 minutes of notification, they will receive a reminder message. At each EMA prompt, participants will be asked to complete self-report items assessed using Qualtrics and then to complete the Emotional Stop-Signal Task on their mobile phone using the Inquisit web platform (Millisecond Software, LLC; available for both iOS and Android platforms). This adapted version of the task also uses negative and neutral stimuli. At the first survey completed each day, the task will have 128 trials (64 negative and 64 neutral trials interspersed). At each subsequent pseudorandom prompt, participants will complete 64 trials (32 negative and 32 neutral trials interspersed) to reduce participant burden while allowing within-person dynamic modeling of changes in affective inhibitory control. The domains assessed using EMA self-report items are listed in Table 2, and specific items are provided alongside the Open Science Framework preregistration [89].

**Table 2 table2:** Domains assessed using self-report ecological momentary assessment items.

Survey and construct		Number of items

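### H3b and H3c date a suicide attempt by the survey that reports it, so an evening or overnight attempt can be scored as following the sleep it preceded or interrupted

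*Protocol article*

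**What the plan says.** Five statements in the protocol article bear on this.

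- **Outcome item.** Table 2 lists, among the items asked at every survey, "Since last survey: suicidal behavior".
- **Survey schedule.** The Intensive Longitudinal Protocol section provides for "7 pseudorandom notifications between specified wake times and bedtimes". On the start of the window it says "We will add 15 minutes to the wake time to avoid missed surveys". The available hours are divided "into 7 equal windows and then randomly choosing a survey time within each bin".
- **Day-level data.** In the Data Analysis Plan, for the sleep models, "survey-level data on SI and SA have been pooled to create day-level variables".
- **H3b model.** Total sleep time on day d-1 "will be used to predict next-day SA (day *d*), controlling for day *d* SI". H3c adds inhibitory control on day d as mediator, predicting SA on the same day d.
- **Claim.** The Hypotheses section states that "short sleep duration will predict greater risk of next-day SA among those with SI".

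The article does not say which night is sleep on day d-1. It states no rule that re-dates, excludes or flags an attempt reported at the first survey of a day.

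**The concern.** H3b is a claim about order: short sleep first, attempt afterwards. The outcome carries the date of the report, not of the event. The first completed survey of day d covers everything since the last completed survey of day d-1, so it takes in the late evening and the whole night. An attempt in that interval enters the model as an outcome of a sleep period that it preceded or broke up. An attempt made during a gap of several days without responses is dated to the day of return.

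An attempt can plausibly change the recording of that night: wakefulness or an emergency visit shortens it, while sedation or immobility lengthens actigraphic sleep. The H3b coefficient would then mix the effect of sleep on attempts with the effect of attempts on sleep, and the sign of the contamination is not known in advance. Adjusting for day d suicidal ideation (SI) does not separate the two, because SI on day d is also measured after an overnight attempt.

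In H3c the mediator is measured only at surveys, so an overnight attempt precedes every day d value of it. Pooling also leaves the order of mediator and outcome open for daytime attempts. H3a is less exposed, because its SI items ask about the current state.

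**Working it through.** **1. The plan's own figure.** The power section gives more than 0.8 for a day-level effect of 0.15 (n=100, t=28). It states no daily outcome rate. A logistic simulation with intercept variance 0.3 (generated, not fitted) gives power of 95% if the outcome occurs on 50% of days, 66% at about 10% of days, and 10% at about 12 attempts in 2,800 person-days. The stated power is therefore reproduced only for a common outcome, and 0.15 is a poor yardstick for bias in a model of attempts.

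**2. The misordered interval.** From the article: 7 equal bins, start at wake time plus 15 minutes, and 64% as the lower compliance in the power section. Assumed: wake 07:00, bedtime 23:00, misses at random.

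- Bin length: 15.75 h / 7 = 2.25 h.
- Full compliance: the last survey falls on average 2.25/2 = 1.125 h before bedtime (about 21:53), and the first at 07:15 + 1.125 h (about 08:23). The first survey's recall window is 10.5 h, of which 1.125 + 8 = 9.1 h lies before waking.
- Compliance p = 0.64: each end moves out by about (1-p)/p = 0.5625 bins, or 1.27 h. The last completed survey is then 2.39 h before bedtime, the window is 13.0 h, and 10.4 h of it lies before waking.

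**3. Share of attempts misordered.**

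| Attempts spread evenly over | Full compliance | 64% compliance |
|---|---|---|
| 16 waking hours | 1.125/16 = 7% | 2.39/16 = 15% |
| all 24 hours | 9.125/24 = 38% | 10.39/24 = 43% |

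The power section assumes 10% of persons with an attempt (stated for H2a), which is about 10 of 100. With one attempt each, the first row gives 0.7 to 1.5 events.

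**4. Consequence, under assumptions.** Null simulations with 10 attempts (n=100, t=28) shortened the affected nights by 1 to 2 within-person SD and counted estimates significant in the H3b direction (z < -1.96, nominal 2.5%). They used ordinary logistic fits, not the planned Bayesian model.

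| Share misordered | Log-odds per SD of sleep | False support for H3b |
|---|---|---|
| 7% | -0.09 to -0.14 | 5-10% |
| 16% | -0.15 to -0.30 | 8-23% |
| 40% | -0.39 to -0.81 | 26-66% |

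With attempts dated to the day they occurred, false support stayed at about 2-3% throughout. Lengthened sleep was not simulated; it would push the coefficient the other way.

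**The case against.** The strongest objection is that sleep on day d-1 is undefined. Sleep is asked about in the morning survey, so the label could mean the night ending on the morning of d-1. The H3b route would then largely close, because that sleep precedes the following evening and night. This stands as a limit on the point. However, the next-day wording favors the night between d-1 and d. The other reading would place a whole waking day between sleep and outcome, and it would not cure H3c, where an overnight attempt still precedes every day d mediator value.

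A second objection is that the exact items, the interview content and the procedures for the 24-hour contact are said to sit with the preregistration and may record event times. That is possible and cannot be checked here. But the article does state the pooling and the lag, and followed as written they break the order. The contact and the interviews are described for risk response and for catching missed events, not for dating the H3 outcome. The same applies to contacts after 1, 2 and 4 days of nonresponse: the gaps are monitored, but the article does not say that attempts in them are dated.

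A reader might infer that H3b is likely to be confirmed by reverse causation, that around 40% of attempts will be misordered, or that the bias exceeds the effect the study can detect. The documents support none of these. They give neither the timing of attempts nor the sleep change on such nights, the sign can go either way, the 38-43% share needs attempts spread evenly through sleeping hours, and step 1 shows why the 0.15 comparison says little with so few attempts.

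**Conclusion.** The point holds as a fault in temporal order with unknown size. On the natural reading of the sleep index, the stated item, schedule, pooling and lag let an attempt count as next-day SA although it came before or during the predictor sleep. For H3c, which the article labels exploratory, the order fails for overnight attempts on either reading.

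On the assumed 07:00-23:00 day, 7% to 15% of attempts confined evenly to waking hours would be misordered, or one or two of about 10, and more if attempts also occur at night. With so few events that can matter, but the simulated inflation depends on assumed shares and sleep shifts and is not a forecast. Because the repair is cheap and H3b is a named hypothesis about order, it should be made before the analysis.

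**What to change.** - Define the sleep-day index: state which night sleep on day d-1 denotes.
- Record the approximate date and time of each SA in the existing contact within 24 hours of a report, or in the 4-week interview. This adds a data item only and leaves the risk procedures as they are.
- In the main H3b and H3c analyses, count as day d SA only attempts that began after the end of the sleep period used as predictor. For H3c, use only inhibitory-control measures taken before the attempt.
- Where an SA first reported at the day's first completed survey, or after a response gap, cannot be dated, set that day's SA to missing in the main analysis, not to a non-event. Report a sensitivity analysis that counts it as day d.

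The cost is one timing question and a recoding rule. Some of the few events may leave the main analysis, especially among the 46 people consented through November 2021 if their event times were not recorded. The first survey's recall window is 10.5 to 13.0 h of 24 (44-54%), so this loss could be substantial where dates are lacking. Attempts during a sleepless night also drop out, although sleep loss may truly have preceded some of them; the report should say so.

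### H3b and H3c let suicidal ideation and inhibitory control measured after an attempt predict that same day's attempt; the main risk is false mediation in exploratory H3c

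*Protocol article*

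**What the plan says.** All of the following is in the protocol article's Data Analysis Plan unless another section is named.

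- **Day-level data.** For the sleep models, "survey-level data on SI and SA have been pooled to create day-level variables". The pooling function is not named, and inhibitory control is not in that sentence.
- **H3b.** Total sleep time on day d-1 "will be used to predict next-day SA (day *d*), controlling for day *d* SI". The text adds: "Models for H3b will parallel those used to test H2a".
- **H3c.** Day d "inhibitory control will be used to predict day" d SA, again with day d SI as covariate.
- **H2a.** "person-mean estimates of SI and person-maximum estimates of SA (yes or no) will be calculated using EMA data". Then: "SA can then be predicted by baseline emotion-related impulsivity and inhibitory control scores using logistic regression analysis, controlling for participants’ SI severity".
- **H2b.** Inhibitory control and SI at time t predict SA at t+1, so order is kept.
- **Items (Table 2).** The SI items ask about the present moment. The suicidal-behaviour item looks back to the previous survey.
- **Task (Intensive Longitudinal Protocol).** The inhibition task follows every survey. "At the first survey completed each day, the task will have 128 trials"; later prompts have 64.

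**The concern.** The hypotheses concern temporal order: which states come before an attempt. H3b and H3c place covariate, mediator and outcome on one calendar day with nothing to order them. Because SI is rated as current while SA is reported in retrospect, even the survey that discloses an attempt carries an SI rating, and then a task score, from after it. Every later survey that day does too.

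An attempt can plausibly change mood, ideation and task performance. The article also has staff contact the participant within 24 hours of a survey reporting suicidal behaviour, which can influence later ratings. If post-attempt values enter the model, an effect of SA on inhibitory control can appear as an effect of inhibitory control on SA, and in H3c as a path from sleep to SA. In H3b and H2a, post-attempt SI in the adjustment set can shift the sleep and baseline effects in either direction.

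**Working it through.** **1. The plan's own figures.** Prompts: 7 × 28 = 196. Events: 10% of n = 100 gives about 10 people with an attempt. One SA day each gives 10 SA days in 100 × 28 = 2,800. The stated detectable OR for H2a (2.63) is closely reproduced by the usual logistic formula, reading 0.3 as a correlation (R² = 0.09): b = (1.960 + 0.842)/√(100 × 0.1 × 0.9 × 0.91) = 2.802/2.862 = 0.979, so OR = 2.66. That figure is not disputed and serves only as a scale.

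**2. Timing, side by side.**

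| Model | SI covariate | Inhibitory control | SA | Order kept? |
|---|---|---|---|---|
| H2b | t | t | t+1 | yes |
| H3b | day d | – | day d | no |
| H3c | day d | day d | day d | no |
| H2a | mean over EMA period | baseline | any in EMA period | covariate no, predictors yes |

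**3. Share of readings at or after the attempt** (assumed: attempts even over prompts, all prompts completed). If SA is reported at prompt k, the share is (8 − k)/7. The mean over k = 1 to 7 is 4/7 = 57%, ranging from 1/7 (14%) to 7/7 (100%). For H2a it is (196 + 1)/(2 × 196) = 50% of an attempter's SI ratings.

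**4. H3c, false positives under no true effect.** Assume that day d inhibitory control is the mean of seven readings with within-day correlation ρ, and that readings at or after the report shift by δ (in SDs of one reading).

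- Mean shift on SA days: δ × 4/7.
- SD of a daily mean: √((1 + 6ρ)/7).
- z = δ × (4/7) × √10 / SD, and rejection rate = Φ(z − 1.96) + Φ(−z − 1.96).

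| ρ | SD | z (δ = 0.5) | rate | z (δ = 1) | rate |
|---|---|---|---|---|---|
| 0 | 0.378 | 2.39 | 67% | 4.78 | >99% |
| 0.2 | 0.561 | 1.61 | 36% | 3.22 | 90% |
| 0.5 | 0.756 | 1.20 | 22% | 2.39 | 67% |
| 0.7 | 0.862 | 1.05 | 18% | 2.10 | 55% |

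Simulation on the same inputs gave 68%, 37%, 22% and 20% for δ = 0.5, and 99% falling to 57% for δ = 1. The nominal rate is 5%. Both checks are single-level simplifications of the planned two-level Bayesian model.

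**5. Size of bias** (simulation of 1,000,000 person-days or persons). Assumed, because the article does not give them: ρ = 0.5, SA on about 2% of days, SI–SA log-odds 0.7 per unit, impulsivity–SI correlation 0.3, sleep to inhibitory control −0.15. The sleep–SI effect of −0.11 is from the article's power section. No true effect of inhibitory control, no direct effect of sleep or impulsivity.

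- H3c, inhibitory control, OR per SD of the daily mean: 1.23, 1.49 and 1.89 for shifts of 0.25, 0.5 and 0.8 SD. At 0.5 SD the false indirect effect is −0.15 × ln(1.49)/0.756 = −0.08 log-odds per SD of sleep.
- H3b, sleep: OR 0.89 to 1.11 for SI shifts of −1 to +1 SD.
- H2a, impulsivity: OR 1.19 to 0.86 for the same shifts.
- Without the post-attempt shift in the values used: 1.00–1.01 (H3c), 0.97–1.01 (H3b), 1.00–1.01 (H2a).

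**6. Cross-reference.** H2a is a between-person logistic regression with one row per person. The sleep paragraph opens by naming two-level random slope models, and the inference paragraph lists H3b with the dynamic models and only H2a as logistic. H2b is the matching model.

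**The case against.** Several stronger readings are tempting, and the article does not support them.

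- **That inhibitory control is averaged over the day.** Only H2a's person-mean SI is explicitly an average. The power section calls inhibitory control day-level but does not say how it is formed, and an article may leave that to a fuller plan. Step 4 is therefore conditional. Even a first-task rule would not fully settle the order, because SA reported at the first survey precedes that task.
- **That one large false-positive rate describes H3c.** The top of the range needs seven same-day readings from one person to be independent. The rate falls steeply with realistic correlation, and full compliance on the day of an attempt is also assumed.
- **That the outcome drives H2a's predictors.** Those are baseline scores, which a later attempt cannot change. Only the covariate described as "controlling for between-person differences in SI severity" is exposed, and the resulting bias is small beside the detectable OR of 2.63.
- **That adjusting for day d SI is over-adjustment.** H3b asks about attempts among people with SI, so conditioning on SI is the intended ideation-to-action question. Replacing it with day d-1 SI to obtain a total effect would change the question. What remains is when SI is measured.
- **That H3b would be fitted as a between-person regression.** The surrounding text makes the model class clear, so the cross-reference is an editorial error.

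It is also fair that H3c, where the risk is greatest, is labelled exploratory. What stands is that the stated models have no ordering rule, although H2b in the same section has one.

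**Conclusion.** The concern holds as a should-fix. As written, H3b and H3c admit SI and inhibitory-control values from after the attempt. The main danger is in H3c, where reverse causation could be reported as mediation: about 20–68% false positives for a 0.5 SD post-attempt shift and 57–99% for 1 SD, over within-day correlations from 0.7 down to 0, if the mediator is a daily mean. For H3b and H2a the bias is modest and its sign unknown (OR about 0.89–1.11 and 0.86–1.19 where the truth is 1, for SI shifts up to 1 SD either way). The timing conflict rests on the article's text. The magnitudes rest on assumed shift sizes and correlations, even timing of attempts and full compliance. A reader might infer that all three analyses are invalid; the modest bias in H3b and H2a does not support that.

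**What to change.** - **H3b and H3c.** Keep SI in the model but preserve order as in H2b. On all days, take day d SI and inhibitory control from one fixed early point, the first completed survey and its 128-trial task, and count as outcome only SA reported at later prompts that day. Leave days with SA at the first completed survey out of the model rather than coding them as attempt-free. Use day d-1 SI as a sensitivity analysis.
- **H2a.** Adjust for SI severity from the baseline interview, at least as a sensitivity analysis to the whole-period EMA mean. EMA SI before the first attempt is not a good substitute: attempters would have a shorter, earlier window than non-attempters. If SI falls linearly after discharge by 0.5 or 1 SD (an assumption), simulation with no true SI–SA link gave a spurious SI OR of 1.13 or 1.28, against 1.00 for the full-period mean.
- **Wording.** Change H3b's parallel from H2a to H2b.

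**Cost.** Variable construction and text only; no new data. SA reported at the first prompt is lost to these models: 1/7 = 14% of SA days if attempts fall evenly, or 1 to 2 of an expected 10. Days with only one completed survey cannot contribute, and a late first survey shortens the outcome window. Baseline SI is a less proximal covariate than SI during follow-up.
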